#### 6.2.2 Secondary Objectives

The secondary objectives of this study are to:

- Compare the positive LV dP/dt max from the multi-vein LV pacing configuration to the standard single spot LV pacing.
- Compare the positive LV dP/dt max from the multi-vein LV pacing configuration to the multispot LV pacing.

- Correlate the (non)invasive measures (blood pressure, electrocardiographic mapping and RV/LV EGM timings) obtained during the three pacing configuration's to the positive LV dP/dt max measures obtained.
- Evaluate the non-invasive measures ability to identify the pacing configuration with the highest positive LV dP/dt max.
- Evaluate the within patient variability in positive LV dP/dt max measures.

## 6.3 Subject Selection

The study is expected to be conducted in approximately 8 centers in Europe and Middle East and Africa (MEA). The study will enroll up to 40 subjects which are required to complete study procedures. It is anticipated this study will require approximately 12 to 18 months for subject enrollment. Patients' participation in this study is expected to last approximately between 1 day and 3 months, pending on the time between enrollment and the EP study and the duration of hospital stay after the research study, an EP related procedure, or the CRT-implant. Subjects must meet all of the inclusion criteria and none of the exclusion criteria to be included in the study.

### 6.3.1 Inclusion Criteria

- Subject is indicated for CRT or CRT-D device according to current applicable ESC/AHA guidelines
- Subject has a left bundle branch block (LBBB) conduction pattern
- Subject is in stable sinus rhythm at the time of the EP visit.
- Subject receives optimal heart failure oral medical therapy (ACE inhibitor and/or ARB and Beta Blockers).
- Subject (or the legal guardian) is willing to sign informed consent form
- Subject is 18 years or older or as specified minimal age per local law/regulation

### 6.3.2 Exclusion Criteria

- Subject has permanent atrial fibrillation/ flutter or tachycardia
- Subject experienced recent myocardial infarction (MI), within 40 days prior to enrollment.
- Subject underwent coronary artery bypass graft (CABG) or valve surgery, within 90 days prior to enrollment
- Subject is post heart transplantation, or is actively listed on the transplantation list
- Subject is implanted with a left ventricular assist device (LVAD)
- Subject has severe renal disease (up to physicians discretion)
- Subject is on continuous or uninterrupted infusion (inotropic) therapy for heart failure ( $\geq 2$  stable infusions per week)
- Subject has severe aortic stenosis (with a valve area of  $<1.0 \text{ cm}^2$  or significant valve disease expected to be operated within study period)
- Subject has complex and uncorrected congenital heart disease
- Subject has a mechanical heart valve

- Pregnant or breastfeeding women, or women of child bearing potential and who are not on a reliable form of birth control
- Subject is enrolled in one or more concurrent studies that would confound the results of this study
- 

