### 7.4.1 Baseline visit

The baseline visit can be a stand alone visit or occur on the same day as the EP study. A subject is enrolled in the study when he/she signs the Informed Consent Form.

At this point, the patient will be assigned a subject number and is considered a subject in the investigation. The following procedures/data collection will be conducted during the baseline visit:

- Verification of all inclusion and all exclusion criteria
- Enrollment
- Subject demographics (e.g., age, gender, height, weight, race)
- Medical history (cardiovascular or related)
- Cardiovascular medications
- NYHA classification
- Blood pressure
- Left ventricular ejection fraction (within last 3 months, otherwise a new measurement should be performed)
- Multi-lead ECG (within last 3 months, otherwise a new ECG should be performed)
- Pregnancy test for women with child-bearing potential
- Echocardiographic evaluation (if available within last 3 months, otherwise not collected )
- Venous blood sample to determine heart failure severity (NTproBNP, creatinine and hemoglobin)
- Magnetic Resonance Imaging (MRI) as explained in paragraph below

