#### **7.4.2 Electrophysiological (EP) study visit**

The EP study visit can be a stand alone visit or can occur on the same day as the baseline visit. The EP study visit should take place within 3 months after the MRI has been obtained. Patients will undergo standard implant of a biventricular pacing system (Medtronic CRT or CRT-D) or will undergo an EP study before possible CRT-implant. If available in the center, a Finger plethysmography system (eg. model Nexfin, BMEYE B.V.) will be connected to one of the subject's fingers to measure the blood pressure non-invasively. In addition, a multi-lead surface ECG is collected during the whole procedure.

Pacing electrodes (cardiac leads or EP catheters) will be placed in the right atrium (RA) and right ventricle (RV). The coronary sinus will be cannulated, a venogram will be obtained and target vessels for LV stimulation will be identified. An EP-catheter ("Multi-electrode lead") or LV lead will be used for LV pacing. Also a CE-certified LV-quadrupolar lead from Medtronic, when available, can be used in the study as an alternative for the EP-catheter. The temporary LV pacing electrodes (EP catheter or LV lead) will be inserted into the coronary sinus (CS) and then sequentially into each suitable target vein.

Targeted myocardial regions for LV lead/catheter placement are: lateral or posterolateral (Standard vein), posterior (Alternative vein I) and anterior (Alternative vein II). Pacing will be performed at up to three spots simultaneously within the Standard vein - MultiSpot), covering the basal to apical locations when feasible (see figure 4). The leads placed in the alternative veins I and II will be stimulated separately or simultaneously (multi-vein; uni-spot) covering the heart circumferentially. A lateral LAO, RAO and/or AP fluoro-screen shot will be taken to document the different (temporary) lead positions.

A Millar pressure catheter or similar will be introduced via the femoral artery retrograde across the aortic valve into the LV for hemodynamic pressure monitoring. Heparin will be administered to ensure that the activated clotting time is monitored per standard hospital practice. The different pacing settings include simultaneous RV- and LV pacing and are in bipolar or unipolar mode.

The MRI-images will ascertain avoidance of pacing ischemic scar tissue. In addition, paced left ventricular QRS-width may also be used for optimal coronary sinus lead placement [33].

A

MRI

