## E Pacing protocol

## Pacing protocol

- Program optimal AV delay
- Turn pacing 'on' via connection box during 10-15 sec
- Turn pacing 'off' via connection box during 10-15 sec
- Repeat ON/OFF 3 times (so 4 times in total)
- Program other AV delays (+/- 20 ms & +/- 40 ms) and repeat pacing protocol

[figure not shown]

**Figure 4: Description of the pacing protocol.** In A the start of the protocol is depicted which involves imaging of the venous anatomy of the patient. The protocol can be separated into two parts, depending on the patient's anatomy. Part B is similar for every patient while part C or D is patient-dependent. In general, one part consists of BiV or Multivein using one or both of two opposite coronary veins (multivein approach). The other part consists of using up to three LV electrodes (BiV or QuadV) to pace from the (postero)lateral vein (multispot approach). Part E is displaying the pacing procedure for 1 out of total 5 AV delays during which the positive  $dP/dt_{max}$  will be measured. Each setting, as indicated by a horizontal line in the figure, will last 10-15 sec. The repetition of steps is used to increase sensitivity of the positive  $dP/dt_{max}$  measurements. Five AV delays will be assessed: optimal AV, optimal AV delay +/- 20 and +/- 40 ms.

At each pacing site, the evaluation of the effect of CRT will be performed approximately 4 times (repetition) in order to increase signal to noise ratio. Each setting lasts about 20 beats (10-15 sec) interspersed with baseline (AAI; also 20 beats, 10-15 sec) pacing. The heart rate will be elevated by atrial pacing to a base rate to 100 bpm or maximally tolerable rate (less than 10% drop in  $dP/dt_{max}$  from baseline no pace), to ensure a constant heart rate. The RV-LV (= VV-timing) intervals will be zero. Optimal AV-delay will be calculated using formulas ( $PAV_{ECG} = \min \{Ap-Pend + 30 \text{ ms}, Ap-RVs - 50 \text{ ms}\}$ ) derived

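### The MI and cardiac-surgery exclusion windows count back from consent rather than from the EP study, so an MI or CABG between separate visits breaches neither dated criterion

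*Combined protocol and SAP*

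**What the plan says.** Section 6.3.2 sets two dated exclusions, repeated in Appendix A: "Subject experienced recent myocardial infarction (MI), within 40 days prior to enrollment" and "Subject underwent coronary artery bypass graft (CABG) or valve surgery, within 90 days prior to enrollment". Section 7.4.1 fixes the reference date for both: "A subject is enrolled in the study when he/she signs the Informed Consent Form".

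The procedure need not follow at once. Section 7.4.2 states: "The EP study visit can be a stand alone visit or can occur on the same day as the baseline visit". Section 6.3 expects participation of about 1 day to 3 months, "pending on the time between enrollment and the EP study" and on the length of the hospital stay.

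Section 7.4.1 lists verification of all criteria as a baseline procedure, and Table 4 ticks eligibility and medical history under Enrollment only. One inclusion criterion in 6.3.1 is tied to the procedure day: "Subject is in stable sinus rhythm at the time of the EP visit".

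Sections 7.5 and 7.5.2 allow the investigator to exit a subject for a medical or other reason. Section 6.5 points to a risk analysis in Section 11, which is not in the supplied text.

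**The concern.** The plan treats an MI in the last 40 days, or CABG or valve surgery in the last 90, as a reason to keep a patient out. The exposure that makes this sensible is the EP study. Section 7.4.2 describes a pressure catheter passed retrograde across the aortic valve, coronary sinus cannulation, heparin and atrial pacing at an elevated rate. Signing consent carries none of that risk, yet consent is the date from which the windows count back.

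When the visits are separate, the written rule can therefore pass a patient it appears meant to stop. The sinus-rhythm criterion shows that the authors could anchor a criterion to the procedure where they chose to.

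A secondary consequence concerns imaging. Section 7.4.2 says: "The MRI-images will ascertain avoidance of pacing ischemic scar tissue". The MRI may be up to 3 months old at the EP study, so an MI after the scan would leave the scar images out of date.

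Patient safety on the procedure day is at stake, not the trial's conclusion.

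**Working it through.** **Date check.** Let consent be day 0 and the EP study day g.

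1. The MI exclusion covers days -40 to 0 and the surgery exclusion days -90 to 0 (6.3.2 with 7.4.1).
2. An event on day x, with 0 < x < g, comes after enrollment, so neither criterion covers it. It is g - x days old at the procedure.
3. Example: with g = 30 and an MI on day 25, the MI is 30 - 25 = 5 days old at the EP study, and the dated criterion is met.
4. Repeating the check on day 30 against the same wording gives the same answer, because the reference date is still day 0. For the same reason, neither the exit ground of unmet criteria (7.5) nor the removal of criteria violations from the primary analysis (8.4) would apply.
5. With same-day visits (g = 0) the problem disappears.

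Valve surgery is partly covered elsewhere: 6.3.2 also excludes significant valve disease expected to be operated on in the study period, and mechanical valves. Neither covers MI or CABG.

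**How many patients.** The documents give neither the distribution of gaps nor event rates. Assume that all 40 patients wait g days and that each event type occurs at 1% to 5% per year. The uncovered days are min(g, 40) for MI and min(g, 90) for surgery.

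Patient-years = 40 × uncovered days / 365.25. Expected events = (MI patient-years + surgery patient-years) × yearly rate.

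| g (days) | MI patient-years | Surgery patient-years | Expected at 1% | Expected at 5% |
|---|---|---|---|---|
| 0 | 0 | 0 | 0 | 0 |
| 14 | 1.53 | 1.53 | 0.031 | 0.153 |
| 30 | 3.29 | 3.29 | 0.066 | 0.329 |
| 60 | 4.38 | 6.57 | 0.110 | 0.548 |
| 90 | 4.38 | 9.86 | 0.142 | 0.712 |

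The 90-day row is an extreme, since the 3 months in 6.3 also include the hospital stay. Under these assumptions every row is an upper bound on patients who would go on to the procedure, because no credit is given for withdrawal, deferral or the valve exclusions.

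**Cost in power of losing a subject.** Section 8.1 uses margin 4, SD 8, true difference 0 and one-sided 0.025. For a paired t-test the noncentrality is (4/8)√n. The plan's figure reproduces: n = 33 gives 79.5% and n = 34 gives 80.8%, and 34/(1 - 0.15) = 40. With 40 analysed, power is 86.9%; with 39 it is 86.1%.

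**The case against.** The strongest reply is that this is a coherent design choice. Section 6.4 places screening before enrollment and 7.4.1 verifies criteria at baseline, so windows counted back from enrollment match that process. That is fair: the documents do not contradict themselves. It does not answer the date check, which turns on what the rule lets through.

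A second reply is that real patients are better protected than the criteria suggest. Appendix A places the measurements before an already planned EP procedure or implant, and for those patients a treating team would ordinarily judge fitness that day. This stands as a mitigation, though section 2 and 7.4.1.1 also allow a dedicated research study, where it would not apply. There are further partial safeguards: the sinus-rhythm criterion, the surface ECG during the procedure, and the limit on atrial pacing "to a base rate to 100 bpm or maximally tolerable rate (less than 10% drop in" dP/dt max. None addresses recent MI or surgery as such.

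A reader might infer from Table 4 that nobody re-checks eligibility on the study day. The table does not show that. It lists data to be collected, and it has no study-day eligibility tick even for sinus rhythm, which must hold at the EP visit. The point rests on the anchor, which a re-check would not cure.

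A reader might also argue that the consent anchor wrongly excludes patients whose MI would be old enough by the procedure. That is only consent timing: the site can take consent after day 40 and, since same-day visits are allowed, proceed promptly.

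**Conclusion.** The point holds for the anchor of these two criteria when the baseline and EP visits fall on different days. An MI or CABG in the interval breaches neither, and the supplied text leaves deferral to discretion. Section 11 is not available, so overall protection is not judged.

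The size is small: 0.03 to 0.55 expected interval events in 40 patients for gaps of 14 to 60 days, resting on assumed rates and on every patient waiting equally long. The share of each window left uncovered depends only on the gap chosen and should not be read as a risk.

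A reader might infer that the primary result is biased. The documents do not support that: Multispot and reference BiV pacing are measured in the same patient during the same procedure, so the within-patient contrast is essentially unaffected. This is a modest patient-safety improvement for the sponsor to consider.

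**What to change.** - In 6.3.2 and Appendix A, count both windows back from the EP study visit instead of from enrollment. The window lengths stay as they are.
- In 7.4.2, when the visits fall on different days, re-verify these two criteria before vascular access, and add a Study day tick for them in Table 4. The baseline check remains as a provisional screen, so the EP date need not be known at consent.
- If a window is breached, defer the EP visit until it has passed, or exit the subject under 7.5. Whether to repeat the MRI after an interval MI can stay a clinical decision.

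The cost is a few words, two yes/no items on the study-day form, and an occasional deferral or exit. A long deferral may overrun the existing 3-month limit between MRI and EP study. There is one consequence for the analysis: a subject studied despite a breach would become a criteria violation and leave the primary analysis under 8.4. Losing one subject this way costs 86.9 - 86.1 = 0.8 percentage points of power.

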## 6.4 Minimization of bias

Potential sources of bias in this study may result from selection of subjects, treatment of subjects, and evaluation of study data. Methods incorporated in the study design to minimize potential bias include but are not limited to:

- Subjects will be their own control, and study measurements have been designed to minimize the impact of within-subject temporal variation.
- Subjects will be screened to confirm eligibility for enrollment with defined inclusion/exclusion criteria prior to enrollment (See Section 6.3 Subject Selection)
- Subject demographics will be collected at the enrollment visit on possible differences that may affect primary endpoints.
- Data collection requirements and study procedures will be standardized across all study centers, including identical and calibrated equipment.
- All implanters in the study will be experienced in the placement of LV leads, performing EP procedures, performing LV pressure measurements.
- All study center personnel and Medtronic personnel will be trained on their respective aspects of the study using standardized training materials. All study clinicians will be trained on and required to follow the Clinical Investigational Plan.

In summary, potential sources of bias that may be encountered in this clinical investigation have been considered and minimized by careful study design.

## 6.5 Data Monitoring Committee

A Data Monitoring Committee will not be utilized for this study considering:

- As a result of risk analysis and mitigation efforts as outlined in Section 11, any residual risk associated with this study is considered low and acceptable.
- All products used in the study (leads and pacing devices) are commercially released (and CE-marked) and used within their intended purpose, except for the Connection Box which is investigational.

An independent Adverse Event Adjudication Committee (AEAC) will be utilized to review and classify the relatedness and severity of all events and deaths.

## 7 Study Visits and Procedures

### 7.1 Center/Investigator selection criteria

All centers that participate in the iSPOT study have to comply with the following minimum requirements:

- Investigator has education / experience in the field of the research (EP procedures and CRT- pacing)
- The center has adequate resources, facilities and equipment at the center to meet the expected enrollment rate.
- The investigator/center has a potential subject population and will be able to enroll approximately 8 subjects in the study
- Investigator has experience in conducting clinical research trials

### 7.2 Center activation

All local and regional regulatory requirements will be fulfilled prior to center activation and enrollment of subjects into the study. Each study site must have written documentation of site and investigator readiness, including (but not limited to):

- Ethics Board approval for the current version of the CIP and Patient Informed Consent (PIC)
- Evidence that the investigator did not participate in the MEC approval
- Competent Authority (CA) approval or notification (if required)
- Current (Co-)Investigator Curriculum Vitae (CV) on file with sponsor (signed and dated)
- Signed/dated Clinical Trial Agreement (CTA) on file with sponsor
- Signed/dated Financial Disclosure form (if needed per country requirements)
- Signed/dated documentation of training of required study personnel

Prior to investigational site activation or subsequent involvement in study activities, Medtronic will provide study training relevant and pertinent to the involvement of personnel conducting study activities and investigator responsibilities. Training will be given on the CIP, the Informed Consent (IC) process, the use of data collection tools, and the database. Study materials will be provided to the site upon investigational site activation.

Medtronic will provide each study center with written documentation of study center/investigator readiness, this letter must be received prior to subject enrollment.

Investigator and/or study coordinator meeting(s) or conference call(s) may be held to discuss the CIP, provide training, discuss study results, etc. Continued training may occur through interim meetings or telephone conference calls to discuss relevant study issues.

### 7.2.1 Equipment Requirements

The following study equipment must be available at each center to support study activities:

- Computer with high speed internet access and Microsoft Internet Explorer available for data entry
- Market released Medtronic programmer (Model 2090)
- Pacing System Analyzer (Model 2290)
- MRI scanner

It is preferable that the following study equipment is available at a center to support study activities:

- Non-invasive beat-to-beat blood pressure monitor (such as Finapres, Finapres Medical Systems, Amsterdam, the Netherlands; Nexfin, Bmeye, Amsterdam, The Netherlands, or similar).

All study equipment must be properly maintained and calibrated if required. Programmer calibration and maintenance will be performed at the Medtronic office in Heerlen, The Netherlands. Only calibrated programmers may be used. Centers are responsible for maintaining and calibrating other equipment not provided by Medtronic and used in the course of this study in accordance with established center practice.

## 7.3 Patient Informed Consent Process

The Informed Consent (IC) process is defined as the process by which an individual is provided information and is asked to voluntarily participate in a clinical investigation (ISO 14155:2011). The Consent Form (CF) is defined as legally effective, documented confirmation of a subject's (or their legally authorized representative) voluntary agreement to participate in a particular clinical investigation after information has been given to the subject on all aspects of the clinical investigation that are relevant to the subject's decision to participate.

At a minimum, each investigational center's Ethics Board will be required to approve the CIP, Investigator's Brochure (IB) and the CF, and any other written study information to be provided to the subjects.

Any changes to a Medtronic and Ethics Board approved version of the CF must be approved by Medtronic and the Ethics Board reviewing the application before being used to consent a prospective study subject. The document(s) should be controlled (i.e. versioned and/or dated) to ensure it is clear which version(s) were approved by the Ethics Board and Medtronic.

Prior to initiation of any study-specific procedures, subjects (or their legally authorized representative) must sign and date the Ethics Board and Medtronic approved CF. The CF must be given to the subject (or their legally authorized representative) in a language he/she is able to read and understand. The principal investigator or authorized designee also must personally sign and date the CF. The process of IC will not be conducted using coercion, or undue influence by the investigator or other center personnel.

The investigator must notify the subject of any significant new findings and answer all questions to the satisfaction of the subject.

The process of obtaining IC shall:

- ensure that the principal investigator or his/her authorized designee conducts the IC process,
- include all aspects of the clinical investigation that are relevant to the subject's decision to participate throughout the clinical investigation,
- avoid any coercion or undue improper influence on, or inducement of, the subject to participate,
- not waive or appear to waive the subject's legal rights,
- use native, non-technical language that is understandable to the subject,
- provide ample time for the subject to read and understand the CF and to consider participating in the clinical investigation,
- include personally dated signatures of the subject or legally authorized representative,
- provide the subject with a copy of the signed and dated CF and any other written information,
- show how IC will be obtained and recorded in circumstances where the subject is unable to provide it him- or herself
- ensure important new information is provided to new and existing subjects throughout the clinical investigation.

The process of IC will not be conducted using coercion, or undue influence by the investigator or other center personnel. The CF must be obtained through a supervised oral process and an independent witness must be present throughout the entire process in the event the patient is not able to read and/or write. The information must be read aloud and explained to the subject. Whenever possible, the subject must also sign and date the IC to attest that the information was accurately explained and that informed consent was freely given.

In the event the subject cannot read and/or write, witnessed (impartial third party) IC will be allowed, provided detailed documentation of the process is recorded in the subject's case history and the witness signs and dates the CF. The original or a copy of the signed CF must be filed in the hospital/clinical chart or with the subject's study documents.

The investigator must document the subject's participation in the medical record. If the IC is obtained the same day the subject begins participating in study-related procedures, it is recommended that it is documented that consent was obtained prior to participation in any study-related procedures.

The CF must be available for monitoring and auditing. Any Medtronic Field personnel who support the study visit must be allowed to review the subject's signed and dated CF and verify its completeness prior to proceeding with the study visit. In the event the Medtronic Field personnel identify a CF as being incomplete, the study visit will not be allowed to occur until the consent of the subject can be adequately and appropriately obtained.

